### Interventions

The intervention treatment period includes 20 sessions over 8 weeks. The participants will visit the research center three times a week through the first 4 weeks and then twice a week through the last 4 weeks. Licensed Korean medical doctors who have at least 4 years of clinical experience will perform the intervention. Detailed information on acupuncture and moxibustion is provided in Additional file 1 and Table 1.

**Table 1 Tab1:** Schedule for treatment and outcome measurements

Period	S	T									Follow-up	
Visit		1	2	3	4–12	13	14	15–18	19	20	21	22
Week		1	1	1	2–4	5	5	6–7	8	8	9	13
Informed consent	●											
Inclusion/exclusion criteria	●											
Laboratory test^a^	●										●	
Vital signs	●	●	●	●	●	●	●	●	●	●	●	●
Demographic characteristics	●											
Medical history/BMI	●											
SRRS	●											
SDTS	●					●					●	
Random allocation		●^b^										
Change of history		●	●	●	●	●	●	●	●	●	●	●
Treatment		●	●	●	●	●	●	●	●	●		
HAM-D	●	●^b^				●^b^					●	●
BDI		●^b^				●^b^					●	●
EQ-5D		●^b^				●^b^					●	●
ISI		●^b^				●^b^					●	●
STAI		●^b^				●^b^					●	●
MYMOP2		●^b^				●^b^					●	●
EEG		●^b^				●^b^					●	●
Pattern identification		●^b^										
Safety assessment		●	●	●	●	●	●	●	●	●	●	●
Blinding test		●								●		

*S* screening period, *T* treatment period, *BMI* Body Mass Index, *SRRS* Social Readjustment of Rating Scale, *SDTS* Screening for Depression and Thoughts of Suicide, *HAM-D* Hamilton Rating Scale for Depression, *BDI* Beck’s Depression Inventory, *EQ-5D* EuroQol-5 Dimension Index, *ISI* Insomnia Severity Index, *STAI* State-Trait Anxiety Inventory, *MYMOP2* Measure Yourself Medical Outcome Profile version 2, *EEG* electroencephalography

^a^Complete blood count and differential count, blood urea nitrogen, creatinine, aspartate aminotransferase, alanine aminotransferase, total bilirubin, albumin, erythrocyte sedimentation rate, thyroid-stimulating hormone, free thyroxine, human chorionic gonadotropin urine test (only for women in their childbearing years)

^b^Before treatment

For the treatment group, disposable, sterilized, filiform needles (Dong-Bang Acupuncture Inc., Seoul, Korea, diameter 0.25 mm, length 40 mm) will be inserted into the skin at the following acupoints: GV20, EX-HN3, GV24, CV17, and bilaterally at LI4 and PC6 [17] (Fig. 2). Practitioners can include up to two additional bilateral acupoints using the outcome of pattern identification based on the theory of traditional Korean medicine. The acupuncture needles will be manipulated to achieve *deqi* and retained for 20 min. During the retaining period, electrical stimulation and moxibustion will be performed simultaneously. An electric acupuncture device (ES-160, Ito Co. Ltd., Tokyo, Japan) will be connected to the GV20 and EX-HN3 acupoints and deliver stimulation with a 10-Hz frequency. Electrical stimulation will be delivered at an intensity that the participant can notice but will still feel comfortable with. For moxibustion, a cylinder-shaped, indirect moxibustion device, Mox-A *Jook Youm* (GuoKu Industrial, Gimpo, Korea, diameter 40 mm, height 50 mm) will be used. The practitioner will ignite two moxibustions. Moxibustions that give off smoke and a scent will be applied to CV12 and CV4 acupoints (Fig. 2).

**Fig. 2 Fig2:**
[figure not shown]
Acupoints for treatment group

The control group will receive sham acupuncture using a Park sham placebo device (PSD, Dong-Bang AcuPrime Ltd., Exeter, UK) [29] on 10 specific nonacupoints (bilateral upper limb 1: topmost point in the middle section of the biceps brachii muscle belly, bilateral upper limb 2: 1.5 cm above upper limb 1 point, bilateral lower limb 1: 1.5 cm above the depression at the midpoint of the upper border of the patella, bilateral lower limb 2: area one third of the way above the medial part of the tibia, bilateral lower limb 3: 1.5 cm above lower limb 2) (Fig. 3). Unlike the real acupuncture needle, the tip of the PSD needle is too blunt to penetrate the skin. The same electric acupuncture device used for the treatment group will be applied for mock electroacupuncture. The electrosimulator will be connected to the PSD needles attached to nonacupoints on both legs (lower limb 2). Electric current will not be delivered, but the device will make the same beeping sounds and create the same light signals as it does for the treatment group [30]. For the sham moxibustion, a hole at the base of the moxibustion will be plugged with Styrofoam to block the channel that transfers heat (Fig. 3). Except for the plugged base, the smoke, scent, and appearance of the sham moxibustion will be the same as that of the real moxibustion. Sham moxibustion will be applied to two nonacupoints on the abdomen (9 cm lateral to the umbilicus) (Fig. 4). These interventions will be performed for the same number of sessions over the same period as the treatment group [31].

**Fig. 3 Fig3:**
[figure not shown]
A front view (**a**, **b**) and a bottom view (**c**, **d**) of real (**a**, **c**) and sham moxibustion (**b**, **d**). Nevertheless, the hole at the base of sham moxibustion is plugged with Styrofoam to block the channel that transfers heat (**d**), the front view of the real and sham moxibustion is undistinguishable

**Fig. 4 Fig4:**
[figure not shown]
Nonacupoints for control group

All participants in both groups will receive a brochure with information about MDD.

### Prohibited and permitted concomitant treatment

Participants will be prohibited from receiving any MDD treatment outside of the interventions of this trial during the 8-week treatment period. If a patient must start medication for MDD due to relapse during the treatment period, they will be withdrawn from the trial. All new treatments started after the beginning of the trial and concomitant medications to treat medical conditions unrelated to MDD will be recorded on the Case Report Form (CRF).

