### Outcomes

The following outcomes will be assessed by independent assessors blinded to the allocation.

The primary outcome measurement of this study is the mean change of total scores in the HAM-D from baseline to the end of the treatment period (week 9). Since its development in the 1960s, the HAM-D has been considered a standard scale to assess MDD severity. The range of the HAM-D score is 0 to 52, with 0–6 indicating normal, 7–17 indicating mild, 18–24 indicating moderate, and 25 or more indicating severe MDD. We will use the validated Korean version of the HAM-D [32].

Secondary outcome measurements include the average change in the HAM-D (from baseline to weeks 5 and 13). The same version of the HAM-D used for the primary outcome measurement will be applied again. In addition, Beck’s Depression Inventory (BDI), the Insomnia Severity Index (ISI), the State-Trait Anxiety Inventory (STAI), the EuroQol-5 Dimension Index (EQ-5D), the Measure Yourself Medical Outcome Profile version 2 (MYMOP2), and electroencephalography (EEG) will be measured as secondary outcomes.

BDI is a multidimensional questionnaire used to assess the severity of the clinical symptoms of MDD. It includes 21 questions to evaluate patients’ cognitive, emotional, and physiological aspects, and the score can range from 0 to 63 points. A higher score indicates a more severe condition [33].

The ISI is an assessment tool designed to diagnose insomnia and evaluate its severity. The range of the score is 0 to 28, with 0–7 points indicating no clinically significant insomnia, 8–14 indicating subthreshold insomnia, 15–21 indicating moderate insomnia, and 22–28 indicating severe insomnia [34].

The STAI is a questionnaire developed by Spielberger et al. in the 1970s. It includes two subscales to assess state anxiety and trait anxiety. Each subscale has 20 items [35].

The EQ-5D is an instrument developed by the EuroQoL group to measure quality of life in terms of health conditions. It includes five items and uses a Visual Analogue Scale to assess overall health conditions [36].

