### Sample size

The purpose of this pilot clinical trial is to explore the efficacy and safety of electroacupuncture plus moxibustion therapy for the treatment of MDD. Based on previous literature [40] (mean difference 4.34, standard deviation 3.75) and assuming a dropout rate of 20%, 15 participants will be assigned to each group.

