### Statistical analysis

Statistical analyses will be performed by an independent statistician blinded to group allocation. Intention-to-treat analysis will be primarily applied in addition to per-protocol analysis. A two-sided test will be used with a significance level of 0.05. Multiple imputation will be adopted when datasets are incomplete.

Sociodemographic information will be presented as the mean ± standard deviation or the frequency (%), and data will be analyzed using Student’s *t* test or the chi-square test. The Wilcoxon rank sum test or Fisher’s exact test will be performed when data are not normally distributed. Analysis of covariance (ANCOVA) will be conducted to compare the mean differences in HAM-D scores between the two groups by substituting each group for factors, points acquired at baseline for covariates, and points assessed at week 9 for dependent variables. RM ANOVA will be performed to analyze the mean change in HAM-D score from baseline to the end of the trial. A paired *t* test or Wilcoxon signed rank test will be applied to compare the average changes between scores assessed before and after treatment. The mean differences of other secondary outcome measurements, such as the BDI, ISI, STAI, EQ-5D, and MYMOP2, will be analyzed following the same methodology as that used in the primary outcome measurement.

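### Participants who start depression medication for relapse are withdrawn from the trial, so on the natural reading their week-9 HAM-D must be imputed in the primary intention-to-treat analysis

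*Protocol article*

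**What the plan says.** All references are to the protocol article.

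- **Prohibited and permitted concomitant treatment.** Other treatment for depression is barred during the 8 treatment weeks. The consequence of needing it is fixed: "If a patient must start medication for MDD due to relapse during the treatment period, they will be withdrawn from the trial". The same section has the CRF record "All new treatments started after the beginning of the trial".
- **Outcomes.** The primary outcome is the change in HAM-D from baseline to week 9, after treatment has ended. On assessment: "The following outcomes will be assessed by independent assessors blinded to the allocation".
- **Statistical analysis.** "Intention-to-treat analysis will be primarily applied in addition to per-protocol analysis". The ANCOVA takes baseline HAM-D as covariate and "points assessed at week 9 for dependent variables". On missing data: "Multiple imputation will be adopted when datasets are incomplete".
- **Table 1** ("Schedule for treatment and outcome measurements"). HAM-D is taken at screening, visit 1, visit 13 (week 5), visit 21 (week 9) and visit 22 (week 13). There is no early-termination column.
- **Sample size.** The planning values are "mean difference 4.34, standard deviation 3.75", with 20% dropout and 15 participants per group.

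Nothing in the article separates stopping the intervention from leaving the trial.

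**The concern.** The rule acts when a participant has done badly on the condition that the primary outcome measures. If withdrawal ends assessment, week-9 scores are lost selectively from those who fared worst. The loss may also differ between arms, since one arm receives sham treatment and neither may take other treatment for depression.

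Intention-to-treat then rests on imputed values for exactly these people. No participant who started medication would have an observed week-9 score from which an imputation model could learn. This is a rule about conduct rather than an analysis detail left to another document: a later analysis plan can choose how to use collected scores, but it cannot supply scores that were never taken.

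The week-13 score would be lost in the same way, as would these participants' later contribution to the repeated-measures analysis. Week 9 also carries the suicide screen (SDTS) and safety assessment, which a relapsing participant has particular reason to keep.

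**Working it through.** **1. The plan's own figure.** The article states no power. With an assumed 80% and two-sided 0.05:

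n per group = 2 × (1.96 + 0.84)² × 3.75² / 4.34² = 11.7, rounded up to 12; 12 / (1 − 0.20) = 15.

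The stated 15 per group reproduces. The 20% allowance covers the number lost, not who is lost.

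**2. What is observed for a relapser.** Table 1 schedules no HAM-D between visit 13 and week 9.

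| Medication started | HAM-D observed before withdrawal |
|---|---|
| Before visit 13 | Screening, baseline |
| After visit 13 | Screening, baseline, week 5 |

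In the second case week 5 is informative only if the worsening had begun by then.

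**3. Shift per excess relapser.** Let D be the amount by which the unobserved week-9 score exceeds the imputed one. The documents give neither D nor a relapse rate, so these are assumed values. One affected participant among 15 moves that arm's mean, and so the group difference, by D/15.

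| Assumed D | D/15 (points) | Divided by unadjusted SE |
|---|---|---|
| −4 | −0.27 | −0.19 |
| 0 | 0 | 0 |
| 4 | 0.27 | 0.19 |
| 9 | 0.60 | 0.44 |

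The unadjusted standard error is 3.75 × √(2/15) = 1.37. If baseline and week 9 correlate at an assumed 0.4, the ANCOVA standard error is about 1.37 × √(1 − 0.16) = 1.25, and the last ratio becomes 0.60 / 1.25 = 0.48.

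Direction: with D positive, an excess of relapsers on active treatment makes imputation flatter the active arm, and an excess on sham does the reverse. With equal numbers and equal D in both arms the shift is zero. D may be near zero or negative if the medication works by week 9.

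**4. How much week 5 helps.** The article gives no imputation model. Assume one using arm, baseline and week-5 HAM-D, with correlations of 0.6 (baseline with week 5), 0.4 (baseline with week 9) and 0.6 (week 5 with week 9). The weight on week 5, given baseline, is

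(0.6 − 0.4 × 0.6) / (1 − 0.6²) = 0.36 / 0.64 = 0.5625.

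If week 5 already shows all of the worsening, a share 1 − 0.5625 = 0.4375 of the shift remains: 0.4375 × 9 / 15 = 0.26 and 0.4375 × 4 / 15 = 0.12. A simulation of 3000 trials per case, with 10 imputations each, gave 0.26 and 0.11. With none of the worsening visible at week 5, or week 5 not reached, it returned about D/15.

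**The case against.** **Non-collection is an inference.** The sentence does not say that assessments stop, and a journal article may leave withdrawal procedures to a full protocol that is not shown. That stands as a limit: a reader might infer that the article states week 9 is not taken, and it does not. Withdrawal from the trial does naturally mean that assessment ends, though, and nothing in the article says otherwise.

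**There is no formal contradiction.** Multiple imputation keeps withdrawn participants in the intention-to-treat set, and 20% dropout is allowed for. This is correct, so the article should not be read as contradicting itself. Neither provision addresses loss that depends on the outcome.

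**Imputation is not blind.** A reader might infer that a relapser's week-9 level can only be assumed. That goes too far: HAM-D and the other scales are measured at visit 13, and step 4 shows that they can remove more than half of the shift. Relapse before visit 13, or worsening after it, remains uncovered.

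**A score after rescue medication may not be the wanted quantity.** The entry criteria and the ban on other treatment suit a comparison without antidepressants. If sham participants need rescue more often and it works, observed scores pull the difference toward zero. This is a real cost of using the scores. It does not argue against collecting them, because collected scores can be set aside and uncollected ones cannot be recovered.

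**Few may be affected.** The trial has 30 participants with HAM-D from 7 to 24 and is exploratory. This limits the priority.

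**Conclusion.** The point holds in a limited form. As printed, the rule removes participants from the trial for a reason tied to the outcome, provides no later assessment, and so on the natural reading leaves their week-9 HAM-D to be imputed in the primary analysis.

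The size and direction of any bias cannot be derived from the article. The 0.27 and 0.60 points per excess relapser rest on assumed values of D, and the reductions from week-5 data rest on assumed correlations and an assumed imputation model. A reader might take 0.44 standard errors as a ceiling. It is not one: it belongs to D = 9, one excess relapser and an unadjusted standard error. Nor do the documents support a claim that the trial is biased in favour of either arm.

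Confidence is moderate, because the full protocol could provide for follow-up after withdrawal. In a feasibility pilot the priority is low to moderate. The change is still worthwhile, because what happens to people who need rescue medication is useful knowledge for designing a full-scale trial.

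**What to change.** Amend the withdrawal sentence to this effect: a participant who must start medication for depression because of relapse during the treatment period stops the trial intervention but, if willing, remains in the trial and attends the week-9 and week-13 visits with the blinded assessor. The medication is recorded on the CRF, as the section already requires for new treatments.

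In the analysis:

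- the observed week-9 score enters the intention-to-treat ANCOVA in the arm as randomised;
- these participants are excluded from the per-protocol set;
- multiple imputation is kept for those who decline the visits;
- an analysis that sets aside scores taken after rescue medication can be shown alongside.

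The cost is one sentence and up to two already scheduled visits for each affected participant. The sample size stays at 15 per group. The downside is that the week-9 score then includes the effect of the medication and may pull the comparison with sham toward zero, which is why the last analysis is useful.

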### Outcomes

The following outcomes will be assessed by independent assessors blinded to the allocation.

The primary outcome measurement of this study is the mean change of total scores in the HAM-D from baseline to the end of the treatment period (week 9). Since its development in the 1960s, the HAM-D has been considered a standard scale to assess MDD severity. The range of the HAM-D score is 0 to 52, with 0–6 indicating normal, 7–17 indicating mild, 18–24 indicating moderate, and 25 or more indicating severe MDD. We will use the validated Korean version of the HAM-D [32].

Secondary outcome measurements include the average change in the HAM-D (from baseline to weeks 5 and 13). The same version of the HAM-D used for the primary outcome measurement will be applied again. In addition, Beck’s Depression Inventory (BDI), the Insomnia Severity Index (ISI), the State-Trait Anxiety Inventory (STAI), the EuroQol-5 Dimension Index (EQ-5D), the Measure Yourself Medical Outcome Profile version 2 (MYMOP2), and electroencephalography (EEG) will be measured as secondary outcomes.

BDI is a multidimensional questionnaire used to assess the severity of the clinical symptoms of MDD. It includes 21 questions to evaluate patients’ cognitive, emotional, and physiological aspects, and the score can range from 0 to 63 points. A higher score indicates a more severe condition [33].

The ISI is an assessment tool designed to diagnose insomnia and evaluate its severity. The range of the score is 0 to 28, with 0–7 points indicating no clinically significant insomnia, 8–14 indicating subthreshold insomnia, 15–21 indicating moderate insomnia, and 22–28 indicating severe insomnia [34].

The STAI is a questionnaire developed by Spielberger et al. in the 1970s. It includes two subscales to assess state anxiety and trait anxiety. Each subscale has 20 items [35].

The EQ-5D is an instrument developed by the EuroQoL group to measure quality of life in terms of health conditions. It includes five items and uses a Visual Analogue Scale to assess overall health conditions [36].

The MYMOP2 is a patient-generated questionnaire. It is optimized to evaluate changes over time for specific health problems specified by patients themselves. The MYMOP2 asks patients to identify their most important symptoms or complaints and rate the severity of the problems. It also asks how they feel about their general wellbeing, how long they have suffered from the problematic symptoms, and whether they take any drugs to attenuate those symptoms [37].

EEG is a method of measuring the electrical activity of the brain by recording the current of electricity captured on the scalp. EEG will be measured for 5 min in a quiet room with the patient sitting on a comfortable chair, and any physical motion will be minimized. Electrodes will be attached at two sites (F3, F4) out of the 10–20-site system of the scalp to evaluate the balance of prefrontal alpha waves from the right and left hemispheres. Previous EEG studies have confirmed that a characteristic, asymmetric pattern of resting frontal activity can be observed in people with MDD that is unlike measurements made in the non-MDD population [38, 39].

Pattern identification is a method to identify and categorize the pattern of clinical signs and symptoms of patients based on the theory of traditional Korean medicine. In this study, the result of pattern identification will be the basis of the choice for optional acupoints. We will also explore whether there is any difference in the tendency between the patterns.

### Sample size

The purpose of this pilot clinical trial is to explore the efficacy and safety of electroacupuncture plus moxibustion therapy for the treatment of MDD. Based on previous literature [40] (mean difference 4.34, standard deviation 3.75) and assuming a dropout rate of 20%, 15 participants will be assigned to each group.

### Statistical analysis

Statistical analyses will be performed by an independent statistician blinded to group allocation. Intention-to-treat analysis will be primarily applied in addition to per-protocol analysis. A two-sided test will be used with a significance level of 0.05. Multiple imputation will be adopted when datasets are incomplete.

Sociodemographic information will be presented as the mean ± standard deviation or the frequency (%), and data will be analyzed using Student’s *t* test or the chi-square test. The Wilcoxon rank sum test or Fisher’s exact test will be performed when data are not normally distributed. Analysis of covariance (ANCOVA) will be conducted to compare the mean differences in HAM-D scores between the two groups by substituting each group for factors, points acquired at baseline for covariates, and points assessed at week 9 for dependent variables. RM ANOVA will be performed to analyze the mean change in HAM-D score from baseline to the end of the trial. A paired *t* test or Wilcoxon signed rank test will be applied to compare the average changes between scores assessed before and after treatment. The mean differences of other secondary outcome measurements, such as the BDI, ISI, STAI, EQ-5D, and MYMOP2, will be analyzed following the same methodology as that used in the primary outcome measurement.

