## Methods/design

### Design

This is a two-armed, parallel-design, patient-assessor blinded, multicenter, randomized, sham-controlled pilot clinical trial. Two clinical research centers in South Korea will conduct the trial: Daejeon Oriental Hospital of Daejeon University and Kyung Hee University Oriental Hospital at Gangdong.

To recruit participants, flyers, daily local newspapers, and advertisement boards at research centers will be utilized. Potential candidates will visit the research centers for screening assessment and to sign informed consent for trial participation after being informed about the aim and details of the study. Eligible participants will be randomly allocated at a 1:1 ratio to one of two arms: electroacupuncture plus moxibustion (treatment group) or sham acupuncture with mock electrical stimulation plus sham moxibustion (control group). Participants will receive treatment for 8 weeks and then visit the research centers twice during a 4-week follow-up period (Fig. 1).

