### Randomization, allocation concealment and blinding

An independent statistician will generate a randomization schedule using SAS (Version 9.4, SAS institute. Inc., Cary, NC, USA). Fifteen subjects will be assigned to each group through the gender-stratified block randomization method. The randomization list will be sealed in sequentially numbered and gender-marked opaque envelopes, delivered to each research center, and stored in a double-locked cabinet. After a candidate participant who meets the eligibility criteria signs an Informed Consent Form, the practitioner will open the corresponding envelope. After the practitioner checks the group allocation for the subject, the envelope will be stored again in a separate, double-locked cabinet. Allocation concealment will be maintained throughout the trial.

It is impossible to blind the practitioners; therefore, they will be excluded from the assessment procedure. All other researchers, such as assessors and data analysts, will be blinded to the group allocation. To confirm that participant blinding was achieved, after both the first and final treatments, assessors will use a “blinding test” questionnaire to ask participants which type of therapy, real or sham, they thought they had been given.

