## Discussion

This is a two-armed, parallel-design, patient-assessor blinded, multicenter, randomized, sham-controlled pilot clinical trial designed to explore the efficacy and safety of electroacupuncture plus moxibustion therapy for the treatment of patients with MDD. Electroacupuncture and moxibustion have been commonly used to treat various psychiatric conditions, including MDD [13]. These treatments exert antidepressive activity by regulating the HPA axis [41], affecting the hippocampus, and influencing dopaminergic and/or serotonergic systems [41, 42]. However, there is little scientific evidence supporting the effectiveness of this combined therapy for MDD. The results of the present study will help to create a foundation for a full-scale RCT to confirm the efficacy and safety of electroacupuncture plus moxibustion therapy for the treatment of MDD patients.

In this study, random allocation will be performed with stratification by gender. Women are more prone to MDD than men [1, 43], with the lifetime incidence of MDD being twice as high in women compared to men [1, 5]. This gender difference is important both for responsiveness to antidepressants as well as for vulnerability to [44, 45], which led to us to stratify participants by gender.

In this trial, EEG was added as an objective outcome to the subjective questionnaires. Previous EEG studies have demonstrated that the brain waves of subjects with MDD differ significantly from those without MDD. There are distinguishable patterns in resting EEG waves between MDD and non-MDD subjects, and activation of the prefrontal alpha waves is more prominent in the left hemisphere than in the right in patients with MDD [38, 39]. The EEG records obtained in this study will be analyzed with a focus on the balance of prefrontal alpha waves between the right and left hemispheres.

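### Allocation is stratified by gender, but the primary ANCOVA adjusts only for baseline score, so its standard error is too large if gender predicts outcome

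*Protocol article*

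**What the plan says.** - **Allocation** (Randomization, allocation concealment and blinding): "Fifteen subjects will be assigned to each group through the gender-stratified block randomization method". Gender is the only stratification factor named.
- **Reason** (Discussion): "This gender difference is important both for responsiveness to antidepressants" and for vulnerability, "which led to us to stratify participants by gender".
- **Primary model** (Statistical analysis): the groups are compared on HAM-D by ANCOVA "by substituting each group for factors, points acquired at baseline for covariates, and points assessed at week 9 for dependent variables". Every term is listed, and gender is not among them.
- **Secondary scales** (Statistical analysis): BDI, ISI, STAI, EQ-5D and MYMOP2 "will be analyzed following the same methodology as that used in the primary outcome measurement", so the omission carries over.
- **Test** (Statistical analysis): "A two-sided test will be used with a significance level of 0.05".
- **Centres** (Design): "Two clinical research centers in South Korea will conduct the trial". The envelopes are "gender-marked opaque envelopes, delivered to each research center, and stored in a double-locked cabinet". The article does not name centre as a stratum and does not say whether each centre has its own list.

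**The concern.** The design and the analysis do not match. Stratified blocks force the arms to be nearly alike in gender, so any outcome difference between men and women largely cancels out of the treatment comparison. The estimate therefore varies less from one randomisation to the next. An ANCOVA without gender cannot credit that gain. It counts the difference between men and women as unexplained noise and reports an interval wider than the design warrants.

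This is more than a detail left to a fuller analysis plan. The article does not stop at naming ANCOVA but assigns a variable to each role in the model.

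Power in a small trial is at stake, and so is the planning of the next one. The pilot is meant as a foundation for a full-scale trial. If gender is prognostic, a residual SD taken from a model without it would be too large for a later trial that adjusts for gender.

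**Working it through.** **1. The plan's own sample size.** Inputs from Sample size: difference 4.34, SD 3.75, dropout 20%. Alpha is 0.05 two-sided. Power is not stated, so 80% is assumed.

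n = 2 × (1.960 + 0.842)² × 3.75² / 4.34² = 2 × 7.85 × 14.06 / 18.84 = 11.7, so 12 per group; 12 / 0.80 = 15.

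The stated 15 per group is reproduced. (85% power would give 18 and 90% would give 20.) The formula has no gender term, so the sample size is not affected by this point.

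**2. Expected size by formula.** Assumptions not in the article: one third men, SD 3.75 within gender, baseline–outcome correlation 0.5, gender unrelated to baseline score. Let the gender difference be d.

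- Residual variance with gender in the model: 3.75² × (1 − 0.5²) = 10.55
- Variance added when gender is left out: (1/3)(2/3)d²
- Approximate SE with 15 per group: √(2 × variance / 15)

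| Gender effect | d (points) | Added variance | Total | SE without gender | Ratio to SE with gender |
|---|---|---|---|---|---|
| 0 | 0 | 0 | 10.55 | 1.19 | 1.00 |
| 0.5 SD | 1.875 | 0.78 | 11.33 | 1.23 | 1.04 |
| 1.0 SD | 3.75 | 3.13 | 13.67 | 1.35 | 1.14 |

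**3. Simulation.** Same assumptions, plus permuted blocks of 4 within gender, no centre effect and 4000 runs per scenario. Each cell gives the planned model, then the model with gender. Power is for a difference of 4.34.

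| Gender effect | Analysed | Mean SE | Type I error | Power |
|---|---|---|---|---|
| 0 | 30 | 1.20 / 1.20 | 4.5% / 4.5% | 93% / 93% |
| 0.5 SD | 30 | 1.24 / 1.20 | 3.9% / 4.6% | 92.5% / 93.2% |
| 1.0 SD | 30 | 1.38 / 1.20 | 2.5% / 4.7% | 89% / 94% |
| 1.0 SD | 24 | 1.55 / 1.35 | 2.7% / 5.0% | 77% / 85% |

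The 24 analysed correspond to the planned 20% dropout (30 × 0.80). A second simulation of the 1.0 SD case with 30 analysed gave SE 1.37 / 1.20, type I error 3.2% / 5.3% and power 88% / 93%. Simulation error on a 5% rate is about √(0.05 × 0.95 / 4000) = 0.3 percentage points, so differences of a few tenths should not be read closely.

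At 1.0 SD the planned estimate actually varies with an SD of about 1.22. Its reported SE of 1.38 is therefore about 13% too large (1.38 / 1.22 = 1.13).

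**4. Centre.** Gender and centre effects of 0.5 SD each, equal centres, 30 analysed, planned model:

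- Centre not a stratum: mean SE 1.29, actual SD of the estimate 1.27 to 1.30. The SE is valid.
- Blocks run separately per centre: mean SE 1.30, actual SD 1.21 to 1.23. The SE is conservative, as for gender.

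**The case against.** The strongest reply is that the two-term ANCOVA is a valid analysis of an exploratory pilot. The error goes in the safe direction, no confirmatory claim depends on the test, and no power is stated. The Discussion speaks of response to antidepressants and of vulnerability. Recent psychotropic drug use is an exclusion, and MDD treatment outside the trial is barred during the treatment period. Nothing in the article shows that gender predicts week-9 HAM-D in this population once baseline is adjusted for.

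Much of this stands. The size is unknown, may be nil, and at a 0.5 SD effect is small. What remains is that the authors thought gender important enough to stratify on and then fixed a model that cannot use it, although including it costs almost nothing.

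A reader might infer two stronger points, and the article supports neither:

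- **That the standard error also ignores a two-centre design, or that centre imbalance biases the estimate.** Centre is not a stated stratum, so leaving it out contradicts no stated design feature. A chance imbalance between centres is ordinary sampling variation that the standard error already covers (step 4). The article does not say that each centre has its own practitioners and assessors. It also does not rule out separate lists per centre, so it cannot be said that centre is unbalanced by design.
- **That the losses are larger, because gender and centre effects add up.** Such figures combine two assumed effects, neither of which has a source in the article, and hide the gender part, which is the only part tied to the stated design.

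**Conclusion.** The point holds for gender. The primary ANCOVA, and with it the analyses of the secondary scales, omits the one factor that the randomisation is stated to be stratified on. If gender is prognostic, the reported standard error is too large, intervals are too wide, the test is conservative and some power is lost. The treatment estimate remains unbiased and false positives are not inflated.

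The size runs from nil to moderate. With 30 analysed, the standard error is overstated by about 3 to 4% at a 0.5 SD gender effect and by about 13 to 15% at 1.0 SD. At 1.0 SD, power falls by about 5 points with 30 analysed and about 8 points with 24. These figures rest on an assumed gender effect, one third men, blocks of 4 and a baseline correlation of 0.5, none of which the article gives. The mismatch between design and model does not depend on them. For centre, the omission affects precision only, unless the lists were generated per centre.

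**What to change.** Before unblinding, specify the primary model as: week-9 HAM-D = group + baseline HAM-D + gender, with gender as a fixed effect and no interaction. Use the same terms, each with its own baseline, for the secondary scales. Keep the two-term model as a sensitivity analysis.

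State whether the randomisation lists were generated separately for each centre. If they were, add centre as a fixed effect. If not, centre is an optional precision term, and whether it is included should be decided in advance.

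The cost is a sentence or two of text and one residual degree of freedom for gender (30 − 3 = 27 becomes 30 − 4 = 26 with all patients analysed). If gender is not prognostic, the mean SE moves only from 1.200 to 1.202. Gender has to be known at allocation in order to pick the envelope, so no new data are needed, and the sample size stays at 15 per group.
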